#### Secondary outcomes

The Inventory of Depressive Symptomatology (IDS-SR) is a 30-item self-report questionnaire that is used to assess the severity of depressive symptoms as reported by the patient [43]. The Clinical Global Impression (CGI) is a 2-item clinician-rated instrument that is used to assess the overall depression severity (CGI-severity), and the general effect of therapy on the overall depression severity (CGI-improvement) [44]. Hedonic capacity is assessed by the Snaith Hamilton Anhedonia and Pleasure Scale (SHAPS), a 14-item self-report questionnaire [45]. The SHAPS assesses hedonic capacity separately from other depressive symptoms, as anhedonia represents a central construct in MDD with multiple aspects, that is often undervalued in current MDD severity measurements [46]. The Beck Scale for Suicide Ideation (BSS) is a 21-item self-report questionnaire that is used to assess the severity of suicidal ideation [47] – separately from other depressive symptoms, as ketamine might reduce suicidal ideation partly independent from its effect on MDD in general [48, 49]. Cognitive functioning is measured by the Autobiographical Memory Test (AMT), involving the presentation of 10 cue words varying in emotional valence. Participants are asked to respond to each cue with a *specific* event that the cue reminds them of [50]. Health related quality of life is assessed by the 5-level version of the EuroQol 5D (EQ-5D-5 L), a self-report questionnaire comprising 5 dimensions (mobility, self-care, usual activities, pain/discomfort, and anxiety/depression), complemented with a visual analogue scale representing general health [51].

Outcomes of adverse events and side effects include the Questionnaire for Psychotic Experiences (QPE) [52], Dissociation Tension Scale (DSS) [53], Iowa Sleep Disturbance Inventory (ISDI) [54], and Systematic Assessment for Treatment Emergent Events (SAFTEE) [55]. Safety and tolerability will also be evaluated via heart rate, blood pressure, weight, and liver enzyme levels testing.

Outcomes that will be used to identify predictors that distinguish patients who can benefit from treatment with oral esketamine include: demographics, the Dutch Measure for quantification of Treatment Resistance in Depression (DM-TRD) [56], the NEO Five-Factor Inventory (NEO-FFI) [57] neuroticism subscale, and the credibility/expectancy questionnaire (CEQ) [58].

#### Additional outcomes

Pain is measured by the Graded Chronic Pain Scale (GCPS) [59], anxiety by the Beck Anxiety Inventory (BAI) [60], and nicotine dependence by the Fagerström Test for Nicotine Dependence (FTND) [61].

We will explore the pharmacokinetics of oral esketamine and its main metabolite esnorketamine, and the genotype of the Cytochrome P450 (CYP) enzymes involved in the metabolism. We will also describe the effects of esketamine on biomarker patterns and gene expression patterns that are related to the pathophysiology of depression [62].

Economic evaluation of treatment with oral esketamine as compared to placebo will be conducted from a societal perspective. A budget impact analysis (BIA) will be conducted to inform decision-makers about the financial consequences of the adoption and diffusion of treatment with oral esketamine for TRD in the Dutch healthcare system.

All measures and associated assessment time points are shown in Table 2.

**Table 2 Tab2:** Schedule of assessments

Measurement instruments	Assessment target	Time points^a^							
		Baseline	Intervention period				Follow-up		
		< T0	T1	T2	T4	T6	T7	T8	T10
Primary and secondary outcomes									
HDRS_17_	Depressive symptoms (clinician-rated)	x		x	x	x	x	x	x
IDS-SR	Depressive symptoms (patient-rated)	x		x	x	x	x	x	x
CGI	Overall depression severity and change	x		x	x	x	x	x	x
SHAPS	Hedonic capacity	x				x			x
BSS	Suicidal ideation	x				x			x
AMT	Autobiographical memory	x				x			x
EQ-5D-5 L	Health related quality of life	x				x			x
QPE	Psychotic experiences	x	x			x			x
DSS	Dissociative features	x	x			x			x
ISDI	Sleep disturbance	x	x			x			x
SAFTEE	Side effects in any organ system	x	x	x	x	x	x	x	x
Physical examination	Heart rate, blood pressure, weight	x	x	x	x	x	x	x	x
Blood collection (I)	Liver enzyme levels	x				x			
Demographics questionnaire	Demographics	x							
DM-TRD	Treatment-resistance	x							
NEO-FFI	Neuroticism	x							
CEQ	Credibility and expectancy of intervention	x							
Additional outcomes									
BAI	Anxiety symptoms	x				x			x
GCPS	Pain	x				x			x
FTND	Nicotine dependence	x				x			x
Blood collection (II)	Biomarkers, gene expression, pharmacokinetics, CYP enzymes	x	x			x			x
Urine collection	Biomarkers	x				x			x
ZGV	Health care consumption	x				x			x

^a^Number illustrates number of weeks after baseline. *AMT* Autobiographical Memory Test, *BAI* Beck Anxiety Inventory, *BSS* Beck Scale for Suicide Ideation, *CEQ* Credibility/expectancy questionnaire, *CGI* Clinical Global Impression, *CYP* Cytochrome P450, *DM-TRD* Dutch Measure for quantification of Treatment Resistance in Depression, *DSS* Dissociation Tension Scale, *EQ-5D-5 L* EuroQol 5D, *FTND* Fagerström Test for Nicotine Dependence, *GCPS* Graded Chronic Pain Scale, *HDRS*_*17*_ Hamilton Depression Rating Scale, *IDS-SR* Inventory of Depressive Symptomatology, *ISDI* Iowa Sleep Disturbance Inventory, *NEO-FFI* NEO Five-Factor Inventory, *QPE* Questionnaire for Psychotic Experiences, *SAFTEE* Systematic Assessment for Treatment Emergent Events, *SHAPS* Snaith Hamilton Anhedonia and Pleasure Scale, *ZGV* Health care use questionnaire (Zorggebruik Vragenlijst) – adapted from the TicP [63] to the context of the current study

### Statistical analysis plan

The efficacy and safety of esketamine will be tested by the use of intention-to-treat and per-protocol linear and logistic mixed models. The effects on biomarker patterns will be tested using Receiver Operating Characteristics (ROC) analyses in combination with phenotype randomization. Pharmacokinetic models will be built by using population pharmacokinetic modelling software (MWPharm) using Iterative-2-stage Bayesian techniques, and will include the absorption (esketamine) or formation (esnorketamine) constant, bioavailability, volume of distribution (relative to bioavailability), and total body clearance (relative to bioavailability). Next, these models will be used to make an estimation of exposure. These data will be analysed using descriptive statistics. The relationship between exposure variables, efficacy and safety will be explored by using regression models and box-and-whisker plots.

EQ-5D-5 L data will be converted into Quality Adjusted Life Years (QALYs) using the Dutch tariffs [64]. Healthcare resource use, loss of productivity, and informal care will be recalculated into societal costs according to the Dutch guidelines for economic evaluation in healthcare [65]. Cost-effectiveness and cost-utility will be reported as incremental costs per point gained on the HDRS_17_ and per QALY gained, respectively. Uncertainty surrounding the outcomes will be assessed by bootstrap analyses and cost-effectiveness acceptability curves.

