#### Statistical power

At the time of sample size calculation, one open-label study had shown antidepressant effects of oral racemic ketamine in 57% of patients [39]. Previously, another open-label study had shown antidepressant effects of oral esketamine in 50% of patients [40]. This indicates a response rate of oral (es)ketamine of 50–57%. As the lack of a control group in these studies might have inflated response rates, in the present trial a response rate of 40% was estimated for the intervention group. For the control group, a response rate of 15% was estimated. This was based on previous studies showing a placebo response in 14.4% of TRD patients [41].

To detect a significant difference in response rate between groups, with the two-sided significance level set at 95% (α = 0.05) and a power of 0.8, 57 participants per group should complete the trial. Assuming a 10% drop-out rate, 64 participants will be included in both groups, leading to a total of 128 participants.

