### Randomization and blinding

Participants are randomly allocated in a 1:1 manner to either treatment group. Randomization is conducted through ALEA Clinical web application. Blinding takes place at the level of participants, clinicians, and study staff. Placebo capsules are matched to esketamine capsules in shape, smell, and colour. All capsules are sealed in identical blisters. Blisters are labelled as trial medication, and given a trial number by the manufacturer ACE Pharmaceuticals. A list with trial medication numbers and the corresponding allocated treatment is stored at the Department of Clinical Pharmacy and Pharmacology of the UMCG. None of the study team members have access to the list until the trial is finished, or unless something unexpected happens that warrants breaking the blind. The success of blinding is tested by asking participants and data collectors at the end of the intervention period which group they thought participants were in, and by comparing these data with the allocation data after unblinding.

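### ROC analysis, the only method named for esketamine's effect on biomarker patterns, fits that aim poorly: it gives no change in marker units and no time course

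*Protocol article*

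**What the plan says.** In the protocol article, the section on additional outcomes sets the aim: "We will also describe the effects of esketamine on biomarker patterns and gene expression patterns that are related to the pathophysiology of depression". The schedule of assessments (Table 2) lists a blood collection for "Biomarkers, gene expression, pharmacokinetics, CYP enzymes" at baseline, T1, T6 and T10. It lists "Urine collection" for biomarkers at baseline, T6 and T10.

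The section headed Statistical analysis plan gives the method in one sentence: "The effects on biomarker patterns will be tested using Receiver Operating Characteristics (ROC) analyses in combination with phenotype randomization". That sentence leaves open:

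- what the ROC curve classifies;
- whether the input is a single value, a change from baseline or a multi-marker score;
- which visits enter.

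The sentence before it reads: "The efficacy and safety of esketamine will be tested by the use of intention-to-treat and per-protocol linear and logistic mixed models". Biomarkers are not named there. The section on randomization adds: "Participants are randomly allocated in a 1:1 manner to either treatment group".

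**The concern.** The aim is a drug effect in a randomized trial with a baseline sample and repeated later samples. The natural estimate is a between-arm difference in the marker, adjusted for baseline, at each visit. The method named instead measures discrimination. What it delivers depends on a class variable that the article does not name:

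- **Class is the randomized arm.** The analysis tests whether the arms separate. It does not say by how much the marker moved in its own units, or when. It draws on the baseline sample only if change scores are the input.
- **Class is a clinical phenotype, for example responder status.** The analysis relates the marker to a state that was not randomized and is observed after baseline, with drug and placebo patients together. That is a correlate of response. Shuffling the labels gives a valid p-value for that association but does not make it an effect of esketamine.

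At stake is the reading of the mechanism-of-action results. A real change in a marker may be missed for want of precision, or a correlate of response may be read as a drug effect. The primary and secondary conclusions are not affected.

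**Working it through.** **The plan's own figure.** The article gives no figure for the biomarker analysis, so the number per arm is taken from the section on statistical power: response of 40% against 15%, two-sided alpha 0.05, power 0.80. With mean proportion 0.275:

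n = [1.96 × √(2 × 0.275 × 0.725) + 0.8416 × √(0.40 × 0.60 + 0.15 × 0.85)]² / 0.25² = 48.9, that is 49 per group.

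With the continuity correction: (48.9/4) × [1 + √(1 + 4/(48.9 × 0.25))]² = 56.6, that is 57. Then 57/0.9 = 63.3, that is 64 per group and 128 in total. The stated 57, 64 and 128 are reproduced, and this point changes none of them.

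**What ROC gives with arm as the class.** The ROC area equals U/(n₁n₀), the Mann-Whitney probability that an esketamine patient's value exceeds a placebo patient's. In a simulated data set both calculations gave 0.6787. Under normality and equal variance the area is Φ(d/√2), which is 0.556, 0.638 and 0.714 for shifts of 0.2, 0.5 and 0.8 SD. So the area does track the standardized effect, but it carries no marker units.

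**Power at one visit.** Assumptions, none of them in the article: a single normally distributed marker, 57 per arm, effect d = 0.4 SD, baseline correlation r.

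- ROC on the on-treatment value: Φ(d√(0.955n/2) − 1.96) = Φ(2.087 − 1.96) = 55%. The factor 0.955 is the efficiency of the rank test relative to the t-test under normality.
- Baseline-adjusted comparison: Φ(d√(n/2)/√(1 − r²) − 1.96). At r = 0.5 this is Φ(2.466 − 1.96) = 69%.
- ROC on change from baseline, whose SD is √(2(1 − r)): Φ(d√(0.955n/2)/√(2(1 − r)) − 1.96). At r = 0.7 this is Φ(2.694 − 1.96) = 77%.
- Efficiency of ROC on the on-treatment value relative to baseline adjustment: 0.955(1 − r²).

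| r | Relative efficiency | ROC, on-treatment value | ROC, change | Baseline-adjusted |
|---|---|---|---|---|
| 0 | 0.955 | 55% | 31% | 57% |
| 0.2 | 0.92 | 55% | 38% | 59% |
| 0.4 | 0.80 | 55% | 48% | 64% |
| 0.5 | 0.72 | 55% | 55% | 69% |
| 0.6 | 0.61 | 55% | 65% | 76% |
| 0.7 | 0.49 | 55% | 77% | 85% |

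**Simulation at a different assumed effect** (0.5 SD, 57 per arm, 4,000 runs per scenario). Type I error was about 5% for all three methods. Power was:

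| r | ROC, on-treatment value | ROC, change | Baseline-adjusted |
|---|---|---|---|
| 0.3 | 73% | 58% | 78% |
| 0.5 | 74% | 74% | 87% |
| 0.7 | 74% | 92% | 96% |

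Baseline adjustment had the most power in each scenario. Its lead ranged from about 4 points (against change scores at r = 0.7) to 22 points (against the on-treatment value at r = 0.7).

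**The case against.** The strongest reply is that in a two-arm trial, with a sentence about effects, the obvious class is the arm. The ROC area is then a legitimate unit-free measure of the between-arm effect, and label permutation gives a valid test. A classifier with permuted labels is also a recognised way to test multi-marker patterns, which is the word the article uses, so power for one marker is an imperfect benchmark. No baseline correlation is given in the article. At low correlation the loss is small, and for skewed or heavy-tailed markers a rank test can beat a normal-theory model. The class variable and the visits used may be set out in a fuller document.

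Most of this stands, and it rules out three stronger readings that a reader might infer:

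- **That the aim is not estimated, or the mechanism question cannot be answered.** This fails if arm is the class, because the test is then valid and the area is an effect measure.
- **That the serial samples are wasted.** The article does not say so. ROC can be run at each visit or on change scores, and the same blood collection also serves pharmacokinetics and CYP enzymes.
- **That the analysis is of responders.** The article does not exclude this, but it does not state it either.

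The reply does not remove the mismatch. The point is not that detail is missing. The article positively names a discrimination method, and no other, for an effect question. Even on its best reading that method gives no difference in marker units and does not by itself model baseline or repeated samples.

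**Conclusion.** The concern holds as a poor fit between aim and method, not as an invalid analysis. With randomized arm as the class, the planned test is valid but less informative than the design allows, and under the assumptions used it is less powerful: about 55% against 64% to 85% for a 0.4 SD effect at r of 0.4 to 0.7. The loss shrinks to about 2 points at r = 0 (55% against 57%). At r = 0.7 it is about 8 points if change scores are used (77% against 85%). These figures rest on normal markers, one visit, 57 per arm, and assumed effects and correlations. With any class other than the randomized arm, the result should not be called an effect of esketamine. Priority is low: this is an additional outcome that the protocol sets out to describe, and it touches neither the sample size nor the efficacy and safety conclusions.

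**What to change.** Replace the sentence on biomarkers as follows:

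- The effect estimate for each marker or pattern score is the between-arm difference from a linear mixed model with arm by visit, the baseline value as covariate, and all scheduled samples.
- P-values across the marker set come from permuting the randomized treatment labels.
- ROC analysis stays as a supplementary analysis of discrimination or response prediction, with its class variable named and the result reported as such.

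The cost is a change of wording and a little more analysis. Skewed markers will need a transformation. No new patients or samples are required, and linear mixed models are already in the plan for efficacy and safety. The change is best made before unblinding.

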In summary, given (1) the advantages of oral over IV administration, and (2) pharmacodynamic arguments for a better antidepressant efficacy of esketamine over racemic ketamine and arketamine, oral esketamine is a promising addition to our currently available treatment armamentarium for depression. To investigate repeated administration of oral esketamine in patients with TRD, we designed a triple-blind randomized controlled trial (RCT).

The primary aim of this RCT is to examine the antidepressant properties of oral esketamine in patients with TRD, as determined using clinician rating scales. Secondary aims involve the effects of oral esketamine on self-reported severity of depression, depressive symptom dimensions, hedonic capacity, suicidal ideation, cognitive functioning, quality of life, safety, tolerability, and its effects in specific subgroups of patients. Apart from these aims, we will address additional relevant questions regarding (1) therapeutic effects of oral esketamine on pain, anxiety and nicotine addiction, (2) its bioavailability and mechanism of action, and (3) its economic impact.

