### Study treatment

Patients randomized to the intervention arm take capsules containing oral esketamine three times a day during 42 consecutive days. During the first 3 days, dosages are gradually increased from 10 mg at administration 1 (day 1) to 30 mg at administration 9 (day 3). During the last 3 days, dosages are gradually decreased from 30 mg at administration 118 (day 40) to 10 mg at administration 126 (day 42). Patients randomized to the control arm take placebo capsules containing microcrystalline cellulose and magnesium stearate. Treatment compliance is assessed during every visit.

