## Discussion

The current RCT examines the effects of repeated administration of oral esketamine as add-on to regular antidepressant medication in patients with TRD. As such, the study addresses the urgent need to identify improved treatment strategies for patients with TRD. The rapid antidepressant effects of IV ketamine have been repeatedly shown in this population, but these effects are mostly transient and the IV administration has disadvantages.

Several study design considerations merit further discussion. Firstly, our trial involves oral rather than IV administration of ketamine. If proven to be effective, oral ketamine poses important advantages over IV ketamine. As previously mentioned, IV administration is costly and impractical. Moreover, it is inconvenient for patients, and associated with more side effects than other routes of administration. This limits the practical utility of IV ketamine in real-world settings.

Compared to IV ketamine, oral ketamine has a variable and low bioavailability of 17–23% [66, 67]. The absorption rate of oral ketamine appears to vary substantially, both between and within patients, possibly due to variation in gut motility, the state of the stomach, food intake, and genetic factors [68]. Additionally, oral ketamine undergoes extensive first-pass metabolism, which is influenced by individual differences in cytochrome phenotypes. While a low bioavailability may negatively influence the efficacy of oral ketamine, the extensive first-pass effects might also have a positive consequence. Namely, norketamine – ketamine’s main metabolite – concentrations are relative high after oral administration of ketamine [68]. In rodent models, norketamine’s antidepressant effects appear to be similar to those of ketamine, but they are associated with less behavioural and biochemical abnormalities [69]. These findings suggest that norketamine might serve as an alternative to ketamine. In our oral (es)ketamine study, we assume that relatively high norketamine levels will be reached during the steady-state phase. Patients might subsequently report similar antidepressant effects with relatively few side effects.

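### Absolute bioavailability is posed as an additional question and listed as a PK model parameter, but oral-only dosing identifies only ka, CL/F and V/F

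*Protocol article*

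**What the plan says.** The last paragraph of the Background section sets out primary and secondary aims. Separately from these, it names additional questions, of which the second is oral esketamine's bioavailability and mechanism: "2) its bioavailability and mechanism of action, and (3) its economic impact".

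The Statistical analysis plan section describes population models fitted in MWPharm by an iterative two-stage Bayesian method. Besides the absorption constant (esketamine) or formation constant (esnorketamine), the models are to include "bioavailability, volume of distribution (relative to bioavailability), and total body clearance (relative to bioavailability"). The models then supply exposure estimates, which are described and related to efficacy and safety.

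Under Study treatment, the only active treatment is oral: "Patients randomized to the intervention arm take capsules containing oral esketamine three times a day during 42 consecutive days". The comparator contains no esketamine: "Patients randomized to the control arm take placebo capsules containing microcrystalline cellulose and magnesium stearate". The Discussion confirms the route: "our trial involves oral rather than IV administration of ketamine".

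Where the article gives bioavailability a value, the sense is absolute, that is, against IV. The Discussion cites a literature range: "Compared to IV ketamine, oral ketamine has a variable and low bioavailability of 17–23"%. The dose rationale, also in the Discussion, assumes 20% to convert an IV dose to an oral one.

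**The concern.** After oral dosing, plasma concentrations depend on F only through the ratios CL/F and V/F. Writing volume and clearance relative to F is the correct response to that fact. Listing F as a further component of the same model is then either redundant or a claim to a quantity the data cannot supply.

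The stake is interpretive. Bayesian software can print a value for F even when the data say nothing about it. The Background section remarks that the bioavailability of oral ketamine has been little studied, then takes up bioavailability as a study question. A reader would take a reported F as an answer, and a value near 20% as support for the figure assumed in the dose rationale, when it would only return what was put in.

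**Working it through.** The article states no figure for this point, so there is none to reproduce. The check is one of structural identifiability.

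**Inputs from the article.** The full dose is 30 mg per administration, three times a day (Study treatment; 90 mg per day in the Discussion). F is 17–23% from literature and 20% assumed (Discussion).

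**Assumptions, for illustration only.** Dosing every τ = 8 h; one compartment with first-order absorption; ka = 1.5 /h, CL/F = 400 L/h, V/F = 1500 L. The conclusion does not depend on these values.

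**Step 1: algebra.** At steady state, with k = CL/V,

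C(t) = (F·D/V) · ka/(ka − k) · [e^(−kt)/(1 − e^(−kτ)) − e^(−ka·t)/(1 − e^(−ka·τ))].

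Here F/V = 1/(V/F) and k = (CL/F)/(V/F). F appears nowhere else, so (F, V, CL) and (cF, cV, cCL) predict the same curve for any c > 0.

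**Step 2: numbers.** Hold CL/F and V/F fixed and vary F. AUC over a dosing interval is D/(CL/F) = 30/400 = 0.075 mg·h/L.

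| F | CL (L/h) | V (L) | AUC (mg·h/L) |
|---|---|---|---|
| 0.10 | 40 | 150 | 0.075 |
| 0.17 | 68 | 255 | 0.075 |
| 0.20 | 80 | 300 | 0.075 |
| 0.23 | 92 | 345 | 0.075 |
| 0.50 | 200 | 750 | 0.075 |
| 1.00 | 400 | 1500 | 0.075 |

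The largest difference between any of these concentration curves and the first was about 3 × 10⁻¹⁸, which is rounding error.

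**Step 3: rank.** The sensitivity matrix of log concentration to (F, CL, V, ka), each on the log scale, at 12 times over the interval has singular values 5.95, 1.97, 0.53 and 4 × 10⁻¹¹. Its rank is 3 of 4. Three quantities are identifiable: ka, CL/F and V/F.

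**Step 4: what depends on F.** Exposure does not: AUC, peak and trough are the same in every row. Absolute CL and V do: from F = 0.17 to 0.23 they change by a factor 0.23/0.17 = 1.35 (92/68 and 345/255). The plan specifies the apparent versions, and these do not move.

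**Step 5: the one way exposure could go wrong.** If F multiplies the dose while clearance is entered as CL/F, AUC becomes F·D/(CL/F). At F = 0.20 that is 0.20 × 30/400 = 0.015 instead of 0.075 mg·h/L, five-fold too low. The article neither says this will be done nor rules it out.

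**The case against.** The article says that the models will include bioavailability, not that it will be freely estimated or reported. F may be a fixed constant, and expressing volume and clearance relative to F suggests the authors know these are apparent parameters. Which parameters are fixed, and on what priors, is detail that a journal article commonly leaves to the full protocol. The word absolute appears in neither the question nor the model sentence, and relative F between patients, occasions or CYP genotypes can be explored once a typical F is fixed. This stands in part: a fixed F would be legitimate, and its absence from the article is not in itself an error. But bioavailability is also posed as a question, and the article's own values for the term are measured against IV. A fixed F does not answer that question.

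Three stronger readings are tempting and should be resisted:

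- A reader might infer that an arbitrary F would contaminate the exposure-efficacy and exposure-safety regressions. It would not: the same concentrations give the same exposure. Only the double use in Step 5 would distort exposure, and with one common F it would rescale all patients alike.
- A reader might take the 35% spread as an error in the trial's outputs. It applies to absolute clearance and volume, which the plan does not specify.
- A reader might say that an aim of the trial fails. The Background section places this question apart from the primary and secondary aims.

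**Conclusion.** The point holds in limited form. As posed, the additional question on bioavailability cannot be answered in the absolute sense by this design, and the parameter list places F beside quantities that already absorb it. The oral data carry no information on absolute F: every value from 0.10 to 1.00 fits equally well. A reported absolute F would reflect a prior or a fixed input and must not be read as confirming the assumed 20%.

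No primary or secondary outcome is affected, nor are CL/F, V/F, exposure or the exposure-response analyses, on the proviso in Step 5. The weight of the point lies in what the trial may claim, so it is worth correcting but modest.

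The conclusion assumes that no IV esketamine data enter the models. The article describes none. The off-label extension, to be described elsewhere, is assumed to add none.

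**What to change.** 1. In the Background section, reword the second additional question as apparent oral pharmacokinetics and systemic exposure (CL/F, V/F, AUC).
2. In the Statistical analysis plan section, drop F as an estimated parameter. Alternatively, label it as fixed or assumed, give its source, and report any quantity that depends on it across the article's 17–23% range.
3. State that F is not applied to the dose when clearance is CL/F.
4. If differences in F between patients, occasions or CYP genotypes are of interest, call them relative bioavailability, with the typical value fixed.

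The cost is a few sentences, with no new samples and no design change. The downside is that the trial gives up any claim to estimate absolute bioavailability, a claim its data could not support.
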